#### Recruitment of staff pre-implementation and post-implementation survey participants and staff post-implementation interview participants

Staff on the participating wards will be recruited to participate in pre-implementation and post-implementation surveys and post-implementation interviews. Staff will be invited to participate via flyers with a URL link and a QR code that take potential participants to the relevant PIS. Following review of the survey PIS, staff can consent to participating, which will then take them to the survey. Staff interested in participating in an interview can contact the study team directly via details on the PIS and flyer. Verbal or written consent will take place prior to the interviews.

#### Recruitment of patient and family member pre-implementation and post-implementation survey and post-implementation interview participants

Potential patient and family member survey and interview participants will be screened for suitability to participate in a survey or interview by clinical judgement of the Nurse Unit Manager of each participating ward. Screening will consider whether participants have sufficient cognitive capability and are medically stable enough to complete the survey and/or participate in a short interview. The Nurse Unit Manager will notify the study team of patients deemed suitable to participate. The Nurse Unit Manager will also notify the study team if a patient has a family member that is suitable to approach in the instances of patients who are not cognitively suitable to participate. A member of the study team will then provide suitable potential participants with a flyer and PIS for the survey or interview. For the survey, participants can select to access the survey via a QR code or request a paper version of the survey for completion. Submission of the electronic or paper survey will indicate their consent to participate in the survey. For the interview, patients and family members will be given at least 12 hours to consider participation after receiving the PIS. A member of the study team will return to the patient’s bedside following this minimum review time and if the patient or family member wishes to participate in an interview, a time for this will be arranged. Written consent will take place prior to the interviews.

Patients with limited English can be invited to participate and consent via use of the culturally and linguistically diverse assist app^36^ and tablet device available on participating hospital wards. An interpreter can be booked via the Health District Interpreter service to translate for survey and interview completion.

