**Figure 2 F2:**
[figure not shown]
Study flowchart. EOI, Expression of Interest.

Staff from nursing, medical, physiotherapy, occupational therapy, dietetics, speech pathology, social work, pharmacy, podiatry, orthotics, diversional therapy, administration and environmental services disciplines working on the participating wards, and inpatients and their family members on the participating wards, will be invited to complete pre-implementation and post-implementation surveys. Given the high turnover of inpatients and staff in many wards and to keep survey responses anonymous, participants in the pre-implementation and post-implementation surveys do not need to be the same. Staff, inpatients and their families will also be invited to participate in post-implementation interviews.

Inclusion and exclusion criteria for the various aspects of the study are provided in table 1.

**Table 1 T1:** Inclusion and exclusion criteria for components of the study

Participants	Inclusion criteria	Exclusion criteria
Hospital wards	Inpatient hospital wards at participating hospitals. Support for nursing and other involved discipline executives to participate in the programme.	Emergency departments. Intensive care units. Paediatric and neonatal wards. Wards currently participating in another research trial with patient falls as a listed outcome. Outpatient settings.
Staff pre-implementation survey participants	Employed by participating hospitals. Work in nursing, medical, physiotherapy, occupational therapy, dietetics, speech pathology, social work, pharmacy, podiatry, orthotics, diversional therapy, administrative or environmental services teams on a ward enrolled to participate in the intervention.	Nil.
Staff post-implementation survey and interview participants	Employed by participating hospitals. Work in nursing, medical, physiotherapy, occupational therapy, dietetics, speech pathology, social work, pharmacy, podiatry, orthotics, diversional therapy, administrative or environmental services teams on a ward that participated in the intervention.	Has worked on the participating ward for <1 week.

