Patient and family member/carer pre-implementation and post-implementation survey participants	Admitted inpatient or family member/carer of admitted inpatient on a participating ward at a participating hospital. Deemed cognitively and medically well enough to participate in a survey as per Nurse Unit Manager of the ward’s clinical judgement. Aged 18 years of age and over.	Inpatient on a ward not participating in intervention. Deemed not cognitively and/or medically well enough to participate in a survey as per the Nurse Unit Manager of the ward’s clinical judgement.
Patient and patient family member/carer interview participants	Admitted inpatient or family member/carer of admitted inpatient on a participating ward at a participating hospital. Deemed cognitively and medically well enough to participate in an interview as per Nurse Unit Manager of the ward’s clinical judgement. Aged 18 years of age and over.	Inpatients or visitors on wards not participating in intervention. Deemed not cognitively and/or medically well enough to participate in an interview as per the Nurse Unit Manager of the ward’s clinical judgement. Has been on ward for <24 hours.

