### Participant recruitment

#### Recruitment of participating wards

Twelve eligible inpatient hospital wards will be recruited to participate in the PROTECT Fall prevention programme and trial via an invitation to voluntarily submit an expression of interest (EOI). The EOI invitation and a participant information statement (PIS) will be circulated via e-mail by a district Fall Prevention and Management Coordinator to the Nurse Unit Managers and Clinical Nurse Educators of the wards of participating facilities. Wards have 2 weeks to decide if they wish to submit an EOI to participate. Ward teams will be provided with the opportunity to ask questions about the study by contacting the research team and by invitations to attend online drop-in information sessions.

If a ward wishes to participate in the study, they will be asked to return a completed EOI form to the study team. The returned EOIs will be screened to ensure they meet inclusion and exclusion criteria. If more than 12 EOIs are received, a selection of wards that optimise diversity of case mix and facility location will be selected. Wards that submit an EOI with a multidisciplinary team will be prioritised. The Nurse Unit Manager of eligible wards will be invited to provide informed consent for their ward to participate in the trial.

We have received a waiver of consent to collect patient outcome data (via routinely collected hospital data) for inpatients admitted to the participating wards during the data collection period.

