### Implementation outcomes and determinants

Implementation outcomes and determinants will be collected for the tailored fall prevention interventions as well as the implementation strategies. These are outlined in table 3 below, which also summarises the evaluation methods. Methods include quantitative surveys and qualitative interviews with key stakeholders to guide lasting implementation and scale-up,^46 48 49^ as well as address questions about barriers to and facilitators of the approach. Observations on wards, file audits and analysis of study records will also be used. Study records include field notes from study staff documenting timing, attendance and notable moods, dynamics and reflections of meetings and education sessions with participating wards. These measures have been informed by McKay’s implementation framework.^49^

**Table 3 T3:** Overview of implementation measures

	Implementation of tailored ward-based fall prevention interventions	Measurement tool	Delivery of multi-faceted implementation strategy	Measurement tool
Implementation outcomes				
Adoption	Proportion and representativeness of participating ward staff that deliver tailored fall prevention intervention.	Ward-specific audits. Staff surveys.	Proportion and representativeness of the sites that use implementation strategies.	Study records. Staff surveys.
Reach	Proportion of patients provided with fall prevention interventions.	Ward-specific audits. Staff surveys. Patient surveys and interviews.	Proportion of eligible wards who submitted EOIs.	Study records.
Dose	Extent of delivery of selected intervention components.	Ward-specific audits. Staff surveys and interviews. Patient surveys and interviews.	Hours per clinical team of delivered multi-faceted implementation strategies.	Study records/fieldwork notes.
Fidelity	Extent to which selected fall prevention interventions are implemented.	Staff surveys and interviews.	Proportion of intended training, education and facilitation sessions provided to and attended by participating clinical teams.	Study records.
Sustainability	Intended ongoing delivery of fall prevention interventions after the 4-month clinical facilitation period.	Staff surveys and interviews.	Participation in peer support sessions after clinical facilitation period has ceased. Intended use of quality improvement skills in future work.	Study records. Staff surveys.
Implementation determinants				

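### The unblinded manager of the ward under evaluation supplies the names of patients and families to survey and interview, so a shift in referral between pre and post can pass for an implementation result

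*Protocol article*

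**What the plan says.** The section on recruiting patient and family participants gives the screening to the Nurse Unit Manager of each ward. The criteria are cognition and medical stability: "Screening will consider whether participants have sufficient cognitive capability and are medically stable enough to complete the survey". Table 1 repeats this as the eligibility criterion for the survey: "Deemed cognitively and medically well enough to participate in a survey as per Nurse Unit Manager of the ward’s clinical judgement". No instrument or threshold is named.

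The manager then passes names on: "The Nurse Unit Manager will notify the study team of patients deemed suitable to participate". Families are reached the same way when the patient is not cognitively suitable: "The Nurse Unit Manager will also notify the study team if a patient has a family member that is suitable to approach". A member of the study team approaches the people so identified.

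The same manager commits the ward to the trial: "The Nurse Unit Manager of eligible wards will be invited to provide informed consent for their ward to participate in the trial". The Blinding section says that ward staff are not blinded.

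Table 1 excludes patients from the interview on the ground "Has been on ward for <24 hours", and excludes staff from the post-implementation survey and interview on the ground "Has worked on the participating ward for <1 week". The patient and family survey row has no minimum time on the ward.

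**The concern.** Screening for capacity by a ward clinician is a normal safeguard. The weak point is that one unblinded person, from the ward being evaluated, applies the screen and also generates the list of people to approach. Under that procedure the study team sees only those referred. It has no independent view of who was suitable but not referred.

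This matters because the comparison is between two separately recruited groups. If referral differs between the pre- and post-implementation surveys, for whatever reason, part of the reported change reflects who was asked. Patient surveys and interviews feed five of the measures in Table 3: reach, dose, acceptability, appropriateness and satisfaction. In a hybrid effectiveness-implementation trial these are results in their own right.

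**Working it through.** The plan states no figure on this point, so there is none to reproduce. The check sets the relevant sections side by side and then shows what the size would depend on.

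**Step 1: can a referral shift enter the result?**
- The study design section says that pre and post survey participants need not be the same, given turnover and anonymity.
- The Survey analysis section tests change from before to after delivery in both staff and patient/family surveys.
- A difference in the mix of people referred is therefore not removed by within-person comparison. It becomes part of the estimated change.

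**Step 2: which measures are exposed?** Sources listed in Table 3 for the tailored fall prevention interventions:

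| Measure | Ward audit | Staff source | Patient survey/interview |
|---|---|---|---|
| Reach ("Proportion of patients provided with fall prevention interventions") | yes | yes | yes |
| Dose | yes | yes | yes |
| Acceptability | no | yes | yes |
| Appropriateness | no | yes | yes |
| Satisfaction | no | yes | yes |

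The Implementation data section says the audits include observation and medical record review. Reach and dose thus have a source that does not pass through the manager's referral. For the other three, the patient view comes only from the people referred.

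**Step 3: is the primary outcome affected?** No. Falls come from the incident management system and coded hospital data under a waiver of consent, with masked adjudication.

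**Step 4: what would the size depend on?** Let s be the share of suitable patients who are referred, and d the mean difference between referred and non-referred suitable patients.

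- Bias in one survey mean = (1 − s) × d.
- Bias in the pre-to-post change = (1 − s_post) × d_post − (1 − s_pre) × d_pre.

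The documents give neither s nor d. Under assumed values:

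| s | d = 0.25 | d = 0.5 | d = 1.0 |
|---|---|---|---|
| 30% | 0.175 | 0.35 | 0.70 |
| 50% | 0.125 | 0.25 | 0.50 |
| 70% | 0.075 | 0.15 | 0.30 |

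If s and d are the same before and after, the change is unbiased. If they move, for example from s = 70%, d = 0.25 to s = 50%, d = 0.5, the change is biased by 0.25 − 0.075 = 0.175 points. An item asked only after implementation has no such cancellation.

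For scale, the Sample size section plans for a 0.5-point change with SD 0.8. Those inputs come from feasibility survey data. The Implementation data section describes piloting for the staff surveys and interview guides only, so their relevance to patient items is not established.

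**The case against.** **The article is condensed.** A sampling order or screening log may sit in the full protocol, so their absence here is not in itself a fault. This stands. The point rests on the procedure that the article does state, in which the manager is the source of names, and for which a better procedure is available at little cost.

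**The text can be read as all suitable patients being notified.** This is a fair reading, and the study team does make the approach. But the text does not require it, and without an independent list nobody could tell whether it happened.

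**Motive.** A reader might infer that managers will favour patients who received or liked the programme. The documents do not support that. They show that the manager consents for the ward and is unblinded. They do not say that the manager leads the ward's project team or knows which patients engaged. The point needs no motive: any change in referral habits is enough.

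**Inflated reach.** A reader might calculate that if true reach is 50% and recipients are twice as likely to be referred, observed reach is 0.5 × 2 / (0.5 × 2 + 0.5) = 67%. The ratio of two is assumed, and the calculation treats reach as read from the patient survey alone, which Table 3 contradicts.

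**A large spurious gain in satisfaction.** This too would need assumed selection at post only. Table 3 defines the measure as satisfaction with the impact of the tailored strategies, which do not exist before implementation, so a pre-to-post shift in that item is doubtful. The items are in a supplement that is not shown.

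**No minimum stay for the survey.** A reader might take this as a further selection bias. It is a question of exposure, not of who the manager refers. Reach is defined over patients without a stay limit, so non-delivery in the first day is genuine non-delivery, and removing such patients would tend to raise measured reach. Before implementation there is no trial programme to be exposed to, and the staff pre-implementation survey has no exclusions either.

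**Conclusion.** The concern holds in a limited form. The stated procedure lets an unblinded manager both decide suitability and supply the names, and the analysis compares separately recruited groups. A change in referral between the two surveys can therefore bias patient-reported implementation measures: chiefly acceptability, appropriateness and satisfaction, and to a lesser degree reach and dose. Referral that is stable over time would largely cancel in change scores.

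The size is unknown. The range of 0.075 to 0.70 points rests wholly on assumed referral shares and differences, and should not be read as an estimate. Nothing here touches the primary outcome. This is a worthwhile, inexpensive improvement and not a threat to the trial's main conclusion.

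**What to change.** In the section on recruiting patient and family participants, change who generates the list:

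1. On each survey day the study team takes the ward's bed list in random or consecutive order.
2. The manager is asked only to rule out patients who are cognitively or medically unsuitable.
3. The team approaches the rest in list order, or a family member where the patient lacks capacity.
4. Each exclusion is logged with its reason.
5. The same procedure is used before and after implementation, and the share ruled out is reported for each.

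The manager keeps the clinical decision. The log does not remove legitimate exclusions, but it shows whether they changed over time.

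No minimum stay should be added to the pre-implementation survey. For the post-implementation survey, at most record time on the ward and report exposure-dependent items with and without patients who had been there under 24 hours.

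Cost: slightly more screening time and a short exclusion log. The study team already goes to the bedside to approach patients.

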## Introduction

 Falls in hospitals remain a common and costly problem for health systems, health staff and patients and their families.^1 2^ They can lead to significant physical injuries and death, especially in older people.^3 4^ Even without injuries, hospital falls can reduce confidence, activity levels and independence, increase length of stay and alter discharge destinations.^5^ No single approach or intervention has proved a solution for this complex problem across broad acute and subacute hospital patient populations.^6^,^8^ This is reflective of the diversity and complexity of patients and contexts in which falls occur.

The recent World Falls Guidelines highlight the need for hospital fall prevention strategies that are tailored to specific environments and personalised for individual patients.^4^ Tailored multicomponent fall prevention interventions, especially those involving patient education, show a promising impact on hospital falls.^9 10^ However, individualised patient education is time-consuming and unlikely to be cost-effective on acute wards with rapid through-put and a lower total proportion of people who fall in hospital.^11^ Large trials of patient education interventions have also had inconsistent results in patients with cognitive impairment.^9 12 13^ Among hospital inpatients aged 65 and over, 29%–38% are estimated to have cognitive impairment.^14^ One study across a large Australian metropolitan hospital found 43% of inpatients over 65 demonstrated cognitive impairment.^15^ The prevalence of inpatients with cognitive impairment is likely to grow with the growing proportion of hospital admissions by older people.^16^

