#### Survey analysis

All returned surveys that have at least one response will be included for analysis. Descriptive statistics (means, SD, change, counts and percentages) will be used to analyse survey data.

Quantitative implementation analysis of survey data will involve numerical description of quantitative implementation measures, presented as percentages or means and exploration with relative risks. Changes from pre-delivery to post-delivery of implementation strategies in self-reported staff and patient/family surveys will be evaluated using paired-sample t-tests. Univariate correlations will explore changes in these measures.

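### The paired t-test named for the surveys does not control for who answered, so a change in respondent mix between waves can enter the pre-to-post difference

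*Protocol article*

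**What the plan says.** All references are to the protocol article.

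- **Who answers the patient/family survey.** Table 1 has one eligibility row for this survey, before and after implementation: "Admitted inpatient or family member/carer of admitted inpatient on a participating ward at a participating hospital". The section on recruiting patients and family members adds that the Nurse Unit Manager tells the study team of "a family member that is suitable to approach in the instances of patients who are not cognitively suitable to participate".
- **Who answers the staff survey.** Study design, randomisation, setting and participants lists "Staff from nursing, medical, physiotherapy, occupational therapy, dietetics, speech pathology, social work, pharmacy, podiatry, orthotics, diversional therapy, administration and environmental services disciplines", which is 13 disciplines.
- **Whether the waves contain the same people.** The same section says that responses are anonymous and that "participants in the pre-implementation and post-implementation surveys do not need to be the same". Table 1 gives one exclusion for the post-implementation staff survey, "Has worked on the participating ward for <1 week", and none for the pre-implementation one.
- **How change is tested.** Survey analysis states: "Changes from pre-delivery to post-delivery of implementation strategies in self-reported staff and patient/family surveys will be evaluated using paired-sample t-tests". It also plans descriptive statistics, relative risks and univariate correlations whose variables are not named. It mentions neither respondent type nor discipline.
- **How the surveys were sized.** Sample size bases them on paired t-tests, with SD 0.8, a mean change of 0.5 Likert points and 80% power. No number of respondents is given.

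**The concern.** A paired t-test removes stable differences between respondents when each person supplies both measurements. With anonymous surveys and no requirement that the same people return, that protection cannot be relied on. The test has no other term that would hold the respondent mix constant.

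The mix could move for ordinary reasons. No quota is stated for patients or relatives, and the share of relatives follows the Nurse Unit Manager's judgement about who is suitable on the ward at the time. Staff opt in through flyers and QR codes. The one-week rule makes the staff waves differ slightly by design. The Introduction puts cognitive impairment at 29% to 38% of inpatients aged 65 and over, and 43% in one Australian hospital, so relatives could be a material share of respondents on some wards.

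At stake are the survey-based implementation measures that have a pre-to-post comparison, and staff professional fulfilment, a secondary effectiveness outcome. Either could appear to improve or worsen because different people answered, and the direction cannot be predicted. In a hybrid trial these results help to explain the fall result, so they need to be readable as change on the ward.

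**Working it through.** **1. The plan's own survey figure.** The stated 80% power cannot be reproduced, because no survey sample size is given. The inputs imply one, if a two-sided alpha of 0.05 is assumed (the article states 0.05 for the fall-rate calculation only):

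- Paired, normal approximation: n = ((1.96 + 0.84) × 0.8 / 0.5)² = 20.1, so 21 pairs. With the t distribution it is 22.1, so 23 pairs.
- Independent respondents, t-based: 41.2, so 42 per wave.

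The 42 per wave serves below as a working size. It is derived here and is not a figure from the article.

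**2. How mix enters the difference.** Let p₀ and p₁ be the share of one respondent group (for example, family members) before and after, and let g be the gap in mean score between that group and the rest. With no true change in either group:

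spurious change = (p₁ − p₀) × g

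It is zero if the mix is stable or if the groups score alike. It does not shrink as more people respond.

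**3. Illustrative sizes.** The article gives neither p₁ − p₀ nor g, so both are assumed. The last column is the two-sided rejection rate with no true change, for a two-sample t-test with 42 per wave and SD 0.8. The article quotes that SD for a paired calculation; using it as a between-person SD is a further assumption.

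| Shift in share | Score gap | Spurious change | Share of 0.5-point target | Rejection rate |
|---|---|---|---|---|
| 10 points | 0.25 | 0.025 | 5% | 5.2% |
| 10 points | 0.5 | 0.05 | 10% | 5.9% |
| 20 points | 0.5 | 0.10 | 20% | 8.7% |
| 20 points | 0.8 | 0.16 | 32% | about 15% |
| 30 points | 0.6 | 0.18 | 36% | about 18% |
| 50 points | 1.0 | 0.50 | 100% | 81% |

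The first row is harmless and the last is extreme. The rates depend on the assumed size: at 100 per wave, the shifts of 0.10, 0.16 and 0.18 points give about 14%, 29% and 35%.

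**4. Would correcting the pairing alone be enough?** No. Suppose the t-test is applied to ward means paired across waves, or replaced by an unpaired analysis that allows for ward. Stable ward differences are then handled, but each ward's mean still depends on who answered in that wave. The expression in step 2 applies unchanged.

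**The case against.** The strongest reply is that this rests on silence. Survey analysis names a test; it does not say that patient and family answers are merged into one estimate, or that staff results will not be broken down by discipline. Strata and covariates are commonly left to an analysis plan, and the article promises a detailed one before analysis begins. This much stands: a reader might infer that each survey will yield a single pooled change and nothing else, and the article does not say so. But the article does fix a test, and that test has no place for respondent type or discipline. The promise of a detailed plan sits under Effectiveness analysis, and Survey analysis does not refer to it.

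A second reply is that a true within-person paired test would largely remove the problem. That is correct, but it requires linking the same people across anonymous waves in which they need not be the same.

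A third is that nothing shows relatives answering on a patient's behalf. This stands. Table 1 makes family members and carers eligible in their own right, and the survey forms are in a supplement that is not shown. A reader might infer proxy reporting, or that relatives see only part of the care; the article supports neither. The Introduction's remark, "Large trials of patient education interventions have also had inconsistent results in patients with cognitive impairment", concerns trial results and not survey scores. The point needs only that the two groups may score differently.

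A fourth is that some measures in Table 3, such as satisfaction with the tailored interventions, may have no pre-implementation value, since those interventions are designed afterwards. This also stands and narrows the reach of the point.

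**Conclusion.** The point holds in a limited form and is worth acting on. As written, the survey test leaves the pre-to-post difference open to changes in who answered, and correcting the pairing alone would not close that gap. Bias requires both a shift in mix and a score gap between groups. The article documents neither, so the bias is possible and not established. It would be wrong to say that a shift in mix is being counted as programme effect.

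The central illustration is 0.10 points, 20% of the 0.5-point target, from an assumed 20-percentage-point shift and 0.5-point gap. Across assumed shifts of 10 to 50 percentage points and gaps of 0.25 to 1.0 points, the range is 0.025 to 0.50 points.

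The effect is confined to survey measures compared before and after implementation, including staff professional fulfilment. The primary fall rate comes from routine hospital data and is not touched.

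**What to change.** In Survey analysis, replace the paired-sample t-test as follows:

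- **Patient/family survey:** estimate the pre-to-post change from a regression on wave with terms for ward and respondent type (patient or family). Show the patient and family results separately as well.
- **Staff survey:** estimate it from a regression on wave with terms for ward and discipline, combining small disciplines by a grouping fixed before the data are examined.
- **Both:** give the respondent mix in each wave, and present the unadjusted wave difference as description only.

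The cost is analysis wording, slightly more analysis and some loss of precision from the extra terms. If the patient/family form does not record who answered, one tick box supplies it for waves still to come. Where respondent type was not recorded in a completed wave, adjustment is not possible for that wave, and this should be stated as a limitation.
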